## Abstract

**Background:**

Approximately 1 in 6 cannabis users develop a cannabis use disorder (CUD) and the odds increase to 1 in 2 for daily users.

**Objective:**

The Dual use of Cannabis and Tobacco Monitoreing through a Gamified Web app (DuCATA_GAM-CaT) project aims to identify cannabis-tobacco patterns of use and withdrawal symptoms among individuals with CUD who are attending substance abuse programs.

**Methods:**

The project uses a mixed methods approach consisting of 3 studies. First, a participatory qualitative study involves focus groups comprising individuals with CUD, clinicians, project researchers, and an expert gamification company to co-design a gamified web app. Second, a longitudinal prospective study to follow up individuals over 6 weeks with CUD attending substance abuse programs . Participants report their cannabis-tobacco usage patterns, type and frequency of tobacco use, nicotine dependence, withdrawal symptoms, psychoemotional factors, and motivation to quit both substances. Predictive analysis techniques are used to analyze clinical, demographic, psychological, and environmental data to predict the probability of achieving abstinence. Third, homogeneous focus groups to explore participants’ experiences during their CUD treatment.

**Results:**

By June 2024, the project had completed the first study, defining eligible cannabis user profiles, developed the initial web app prototype, and initiated recruitment across 10 centers, with 74 participants enrolled, aiming to reach 150 participants in total.

**Conclusions:**

All participants are required to provide informed consent, and their information is kept confidential and anonymized following confidentiality rules. The research team is committed to disseminating the results obtained to professional and patient groups, as well as informing public health agents, to positively influence political and social decision makers and design programmers. Additionally, we aim to prioritize the publication of the results in high-impact journals specialized in drug abuse, public health, and health care services research.

**Trial Registration:**

ClinicalTrials.gov NCT05512091; https://clinicaltrials.gov/study/NCT05512091

**International Registered Report Identifier (IRRID):**

DERR1-10.2196/58335

## Introduction

### Cannabis and Tobacco Use

Cannabis has emerged as the most widely used illegal drug globally [1]. In Spain, it also holds the status of the most commonly used illegal drug. According to the latest survey conducted in Spain in 2019, 37.5% of adults aged 15-64 years have experimented with cannabis at some point in their lives, with 10.5% reporting usage in the last month (men: 11.4% and women: 4.7%) [2]. Furthermore, approximately 1 in 6 cannabis users develop a cannabis use disorder (CUD) and the odds are increasing to 1 in 2 among daily users [2].

In Western countries, cannabis use is commonly intertwined with tobacco**,** resulting in a significant prevalence of combined usage that continues to rise [3]. For instance, in the United States, the daily use of both substances remained stable over the years from 2005 to 2014, with a usage percentage of 6%. This proportion is higher than that of individuals who consume only cannabis without tobacco, which is around 2% [4]. However, it is important to note that dual cannabis and tobacco use, or co-use, can manifest in various patterns such as (1) concurrent use, where both substances are consumed simultaneously in the form of joints, which is the most prevalent form of cannabis use in Europe [3,5,6]; (2) sequential concurrent use, involving the use of cannabis followed by tobacco or vice versa; (3) asynchronous concurrent use, characterized by cannabis and tobacco usage within the past month but not necessarily during the same instance of consumption; and (4) exclusive cannabis use, where tobacco is not involved [4].

Moreover, dual cannabis-tobacco use entails a nuanced description of dependence diagnosis for both substances collectively and individually, alongside the emergence of withdrawal symptoms, particularly when cannabis consumption is reduced or halted [7-9]. Cannabis withdrawal symptoms typically manifest within 2 to 4 days after a reduction or cessation of consumption, peak during the first week, and may persist for up to 4 weeks [10]. The cannabis withdrawal syndrome is recognized and included in the *DSM-5* (*Diagnostic and Statistical Manual of Mental Disorders* [Fifth Edition]) [11]. It is characterized by symptoms such as irritability, anger or aggression, nervousness or anxiety, sleep difficulties (eg, insomnia and disturbing dreams), decreased appetite or weight loss, restlessness, depressed mood, and at least one of the following physical symptoms causing significant discomfort: abdominal pain, shakiness or tremors, sweating, fever, chills, or headache. The symptoms can be assessed using the “Cannabis Withdrawal Checklist” scale. While this scale has been validated [12] and used primarily in English-speaking populations [13-16], its applicability elsewhere warrants consideration.

A meta-analysis has estimated that 47% of cannabis users experience withdrawal syndrome upon cessation, with its occurrence often linked to tobacco use [9]. Additionally, the severity of the cannabis withdrawal syndrome inversely affects the likelihood of successful cessation, with more severe symptoms correlating with lower rates of quitting [9]. Given that cannabis withdrawal syndrome frequently contributes to relapse [17], resulting in modest rates of abstinence maintenance, it is noteworthy that only 30% of individuals who undergo treatment manage to sustain abstinence during the initial month [18]. Various factors contribute to relapse, including the use of other psychoactive substances [19], psychological variables (emotions, social pressure, etc), perceptions of social norms, self-efficacy [20], and sociodemographic variables (sex, age, ethnicity, etc) [16].

### Cannabis and Tobacco Dependence Withdrawal Syndromes

The limited number of studies conducted on individuals undergoing treatment for CUD who also use tobacco fail to provide sufficient insight into the interaction between the consumption patterns of both substances. Consequently, there exists a potential misclassification of withdrawal syndromes between cannabis and tobacco [10,21]. As a result, the influence of cannabis and tobacco dependence, along with their respective withdrawal syndromes, on cannabis use remains unclear, particularly in conjunction with other cognitive and environmental factors previously associated with substance use and cessation. Drawing from the social science literature and conceptual models that aid in understanding individual behaviors, we propose using the Attitudes, Social Influences, and Efficacy (ASE) model [20] to decipher the factors affecting cessation and maintenance processes. Therefore, we integrate this model [20] with individual attributes (such as sex, age, and socioeconomic status) and addiction characteristics (smoking pattern, dependence, etc) to unravel this intricate phenomenon (see Figure 1).

**Figure 1 figure1:**
[figure not shown]
Logic model of the study. ASE: Attitudes, Social Influences, and Efficacy.
de Vries H, Backbier E. Self-efficacy as an important determinant of quitting among pregnant women who smoke: the
phi-pattern. Prev Med. 1994;23(2):167-174. [doi: 10.1006/pmed.1994.1023] [Medline: 8047522].

The lack of a detailed characterization of the influence of tobacco and cannabis use is partly due to the absence of techniques enabling real-time assessment, such as Ecological Momentary Assessment (EMA) [22]. While these powerful tools have been used to characterize and predict patterns among individuals with alcohol use disorder [23,24], they have yet to be used among cannabis users. Consequently, the combination of these tools could facilitate the characterization of the prevalence and patterns of dual cannabis-tobacco consumption, including a detailed description of the severity and types of symptoms experienced by users during cannabis withdrawal syndrome.

Consequently, due to limited knowledge regarding (1) how tobacco impacts cannabis withdrawal syndrome and (2) the effect of dual consumption on dropout probabilities during CUD treatment, we propose the Dual users of Cannabis and Tobacco (DuCATA) study. This mixed methods project encompasses 3 studies (qualitative, quantitative, and mixed methods) with a clinical and epidemiological focus, enabling the characterization and monitoring of consumption and withdrawal syndromes of cannabis and tobacco among individuals initiating treatment for CUD. The monitoring of dual cannabis-tobacco use and withdrawal symptoms will be conducted via a prospective follow-up of participants using a gamified web app [25] based on the EMA model [22,26] facilitating real-time collection of participants’ consumption and symptoms based on their daily experiences. Gamification, through the incorporation of gaming elements, encourages active user participation in data reporting, thereby enhancing adherence to the registry and improving data quality [25].

This knowledge bears significant implications for clinical practice and public health, as it will provide precise insights into the characteristics of dual cannabis-tobacco users, a profile increasingly prevalent in programs. Moreover, it will enable us to use and validate an instrument developed in April 2023 for monitoring cannabis withdrawal symptoms among the Spanish population and investigating nicotine dependence. Ultimately, we are confident that comprehending and describing the dual use of cannabis-tobacco will equip future studies with a tool to accurately assess this complex phenomenon and facilitate the design of tailored interventions.

### Study Objectives

#### Overview

The research aims of the “Characterization of the pattern of consumption and withdrawal syndrome of dual use of cannabis and/or tobacco in people with CUD who start cessation treatment: DuCATA study” can be described, indicating the studies in which each objective falls.

#### Objective 1 (First Study)

Determinate the treatment preferences of individuals with CUD, based on age (18-34 years and 35 years or older) and sex, for the design of a gamified web app.

#### Objective 2 (Second Study)

Examine the consumption patterns of cannabis and tobacco products among individuals seeking help to reduce and quit their cannabis use. This includes considering structural determinants of inequality (age, sex, social class or educational level, and territory) and clinical history (use of other substances, psychiatric comorbidity, etc), and identifying different typologies of cannabis-tobacco users, such as concurrent use, sequential use, asynchronous use, and exclusive cannabis use.

#### Objective 3 (Second Study)

Analyze changes in tobacco use during the cannabis treatment process based on the identified typologies of cannabis-tobacco users and the level of clinical care they receive (with or without assistance for quitting tobacco).

#### Objective 4 (Second Study)

Validate the “Cannabis Withdrawal Checklist” scale in the Spanish population and explore the relationship between the intensity and duration of craving and abstinence.

#### Objective 5 (Second Study)

Describe and predict the likelihood of cannabis and tobacco abstinence based on consumption patterns (eg, type of consumption), psychological factors (trait and state), and contextual factors (eg, environment, social influences, and activities) while considering structural determinants of inequality.

#### Objective 6 (Third Study)

Investigate the clinical experiences of individuals undergoing treatment for CUD, taking into account their typologies, age, and sex.

In conclusion, the “DuCATA study” aims to achieve 6 objectives across different studies. These objectives involve understanding treatment preferences for CUD through a gamified web app, examining the patterns of cannabis and tobacco use among individuals seeking help, validating assessment scales, and exploring clinical experiences.

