## Methods

### Project Design

The project adopts a sequential mixed methods research design encompassing 3 studies. The first study, a qualitative participatory action study aimed at addressing objective 1 by exploring key elements pertinent to the co-design of the gamified web app. The second study is a prospective longitudinal (cohort) study targeting objectives 2 to 5 to quantitatively examine implementation and effectiveness outcomes. The third is a qualitative phenomenological study addressing objective 6 to delve into participants’ experiences within the project. This integrated approach enables a comprehensive investigation into the patterns of consumption and withdrawal syndrome associated with dual cannabis and tobacco use among individuals undergoing cessation treatment for CUD, synthesizing qualitative insights with quantitative findings to provide a holistic understanding of the research objectives.

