### Third Study: Assessment of the Acceptability of the Web App

#### Objective

The objective is to evaluate the acceptability of the web app and investigate participant and clinician experiences during study 2, focusing on implementation outcomes.

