#### Sample

Participants will be selected from study 2 cohort members based on their web app usage experience. A total of 4 groups comprising 5-7 participants each are anticipated.

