#### Recruitment

Purposive sampling will be used, targeting individuals meeting the inclusion criteria and having engaged with the web app. Homogeneity criteria will be applied to ensure diversity across fidelity levels and gender—group 1: high fidelity male users; group 2: low fidelity male users; group 3: high fidelity female users; and group 4: low fidelity female users.

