#### Main Themes

The main themes are exploration of barriers and opportunities encountered during web app usage, assessment of the use of web app monitoring for cannabis or tobacco use and mood, and identification of preferred and disliked features of the web app.

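### Study 3 is designed to evaluate the web app, not to address Objective 6 as worded, and it samples no clinicians although its objective names them

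*Protocol article*

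**What the plan says.** Three places state what Study 3 is for. Objective 6 in the Study Objectives reads "Investigate the clinical experiences of individuals undergoing treatment for CUD, taking into account their typologies, age, and sex". The abstract's Methods describe "homogeneous focus groups to explore participants’ experiences during their CUD treatment". Project Design says "The third is a qualitative phenomenological study addressing objective 6 to delve into participants’ experiences within the project". No other study is assigned to Objective 6.

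The section on the third study, titled as an assessment of app acceptability, then sets out the design:

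- **Objective:** to "evaluate the acceptability of the web app and investigate participant and clinician experiences during study 2, focusing on implementation outcomes".
- **Sample:** "Participants will be selected from study 2 cohort members based on their web app usage experience", in four groups of 5 to 7.
- **Recruitment:** people must have engaged with the app. The groups cross fidelity with gender: "group 1: high fidelity male users; group 2: low fidelity male users", and the same two for women.
- **Main Themes:** "exploration of barriers and opportunities encountered during web app usage", the use of the app to monitor consumption and mood, and which app features were liked or disliked.
- **Data Analysis:** the results will be used to refine the app prototype.

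**The concern.** The objective and the methods describe two different enquiries. One asks how people live through treatment for cannabis use disorder and how that differs by pattern of use, age and sex. The other asks how people found the app. A study can do both, but the elements that fix what will be learned (who is selected, how they are grouped, what they are asked, what the answers are for) are all set for the second.

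If the study runs this way, one of the project's six objectives has no planned topic on its subject and no sampling rule for two of its three axes. Clinicians' experience, which the Study 3 objective promises, would have no source. Readers of the eventual report would expect findings on treatment experience by typology and receive findings on app usability by fidelity.

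**Working it through.** No power or error-rate figure is involved. The check sets the stated aim beside the stated design and adds simple counts.

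**1. Aim against design**

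| Element | Objective 6 / abstract | Study 3 methods |
|---|---|---|
| Subject | Clinical experience of treatment | App acceptability and implementation outcomes |
| Who | People in treatment for cannabis use disorder | Cohort members who engaged with the app, chosen on usage |
| Typology | Required | Not mentioned |
| Age | Required | Not mentioned |
| Sex | Required | Covered by male and female groups (labelled gender) |
| Themes | Treatment experience | 3 of 3 main themes concern the app |
| Use of findings | Understanding clinical experience | Refinement of the app prototype |

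One of the three axes is built into the groups. The subject itself is not among the main themes.

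**2. Clinicians**

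The Study 3 objective is to "evaluate the acceptability of the web app and investigate participant and clinician experiences during study 2". The Sample section draws on cohort members, and the Cohort Members section in Study 2 defines these as cannabis users beginning treatment. All four groups in the Recruitment section are groups of users. Clinicians in the stated Study 3 sample: 0. The sessions with clinicians under Study 1 (Data Collection Technique) served user profiling and app design before the cohort began, so they cannot supply experience of Study 2.

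**3. Size of the sample against the axes**

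Inputs: 4 groups of 5 to 7 (Study 3, Sample); 4 typologies (Cannabis-Tobacco Users' Classification); 2 sexes. Two age bands, 18-34 and 35 or older, are given for Objective 1 only; using them for Objective 6 is an assumption.

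- Participants: 4 × 5 = 20 to 4 × 7 = 28.
- Typology × sex: 4 × 2 = 8 cells, averaging 20/8 = 2.5 to 28/8 = 3.5 people.
- Typology × sex × age: 4 × 2 × 2 = 16 cells, averaging 20/16 = 1.25 to 28/16 = 1.75 people.
- Typology × age inside each fidelity-by-gender group: 4 × 2 = 8 combinations for 5 to 7 people. Over four groups that is 32 combinations for at most 28 people, so the full grid cannot be filled.

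Focus groups do not need filled cells. The counts show two things: without a sampling rule nothing ensures that a given typology or age band is heard at all, and a remedy that demanded a full grid would be unworkable.

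**The case against.** **A condensed article.** The list is headed as main themes, and a full topic guide may exist elsewhere. This would answer a complaint about missing detail. It does not remove the conflict, because selection, grouping, themes and use of findings are all stated and point away from the stated objective.

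**A looser reading of Objective 6.** Project Design glosses it as experiences within the project, close to the Study 3 objective, and cohort members are in treatment. This has some force: the document supports two readings. But the abstract and the objective itself say treatment experience, while the Study 3 objective narrows experience to implementation outcomes. The readings still have to be reconciled.

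**Typology and age are already known.** Participants come from Study 2, where both are recorded, and Objective 6 asks only that they be taken into account. That stands: groups need not be formed on them, and a descriptive comparison at analysis would do. It helps only if treatment experience has been discussed.

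**Stronger readings.** A reader might infer that Study 3 will produce no data at all on Objective 6. The documents do not support this: sex is built into the groups, the monitoring theme touches consumption and mood during treatment, and participants may speak of their treatment unprompted. A reader might also infer that the mixed-methods integration has nothing to work with. That does not follow either. Project Design and Main Findings promise synthesis and triangulation in general terms, not the linking of typology to experience, and Implementation Outcomes provides quantitative acceptability and adherence data to set beside the focus groups.

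**Conclusion.** The point holds as a contradiction within the article: Study 3 as written is not designed to address Objective 6 as worded. One of three axes is covered, none of the three listed main themes is treatment experience, and no clinicians are sampled despite being named in the objective. The conclusion assumes that the listed themes represent the planned discussion and that gender in the grouping stands for sex in the objective.

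The reach is limited. Study 3 is a qualitative component of 20 to 28 people, and Study 2 and Objectives 2 to 5 are unaffected. It is worth correcting because the change is cheap and Study 3 follows the end of Study 2, with a scheduled start of January 2025, so no cohort data need to be touched.

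**What to change.** Choose one of two routes before Study 3 starts.

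- **(a) Bring the design to the objective.** Add experience of treatment for cannabis use disorder to the main themes. Keep the four groups, and when inviting people use Study 2 data to seek variation in typology and age within each group, without requiring every combination to be filled. Report findings by typology, age and sex descriptively. State that requiring app engagement limits the conclusions to app users.
- **(b) Bring the objective to the design.** Restate Objective 6, the closing summary of the objectives and the abstract as app acceptability and experience within the project.

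Under either route, include the collaborating clinicians in Study 3 or delete the reference to clinicians from its objective.

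Route (a) costs a slightly longer topic guide and some care in selecting invitees, with the same number of user groups. Route (b) costs only text, at the price of a narrower stated objective. Including clinicians would add some data collection; deleting the reference would not.

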## Methods

### Project Design

The project adopts a sequential mixed methods research design encompassing 3 studies. The first study, a qualitative participatory action study aimed at addressing objective 1 by exploring key elements pertinent to the co-design of the gamified web app. The second study is a prospective longitudinal (cohort) study targeting objectives 2 to 5 to quantitatively examine implementation and effectiveness outcomes. The third is a qualitative phenomenological study addressing objective 6 to delve into participants’ experiences within the project. This integrated approach enables a comprehensive investigation into the patterns of consumption and withdrawal syndrome associated with dual cannabis and tobacco use among individuals undergoing cessation treatment for CUD, synthesizing qualitative insights with quantitative findings to provide a holistic understanding of the research objectives.

### Ethical Considerations

The study protocol has been reviewed and approved by the Hospital Universitari de Bellvitge Ethics Committee (PR328/19) and registered on ClinicalTrials.gov (NCT05512091) [27]. The research complies with institutional guidelines and adheres to Law 3/2018 of Personal Data Protection and the General Data Protection Regulation 2016/679 of the European Union. All participants have provided or will provide informed consent before participating in the study. They have been or will be informed of their right to drop out at any time without any negative consequences. For any secondary analyses using existing data, the original consent includes permission for secondary analysis without the need for additional consent. The confidentiality of all information has been or will be ensured, and the research team has adhered to or will adhere strictly to confidentiality rules. Data will be anonymized to protect participant privacy. If data cannot be anonymized, protective measures will be in place to safeguard participant information. Participants do not receive monetary compensation for their participation. Instead, they are thanked and acknowledged for their valuable contribution to the research.

